### Project Phases and Study Design

3.1

Each phase of the project will use different quasi‐experimental designs. Table 1 presents a summary of the study design, population, setting, variables, sample size, and study period for each phase.

**TABLE 1 fsn371640-tbl-0001:** Study designs, study populations, study settings, study variables, sample size and estimated study periods for each phase of the project.

	Project phases			
	Phase 1	Phase 2	Phase 3	Phase 4
Study design	Three‐arm pre‐post parallel design	Four‐arm placebo‐controlled single‐blind pre‐post parallel design	Four‐arm placebo‐controlled single‐blind pre‐post parallel design	Two‐arm placebo‐controlled, single‐blind (participants), parallel feasibility trial
Study population	Healthy‐weight adults living in Australia	Healthy‐weight adults living in Australia	Overweight or Obese adults living in Australia	Overweight or Obese adults living in Australia
Study setting	Laboratory‐based	Laboratory‐based	Laboratory‐based	In a natural environment (at home)
Independent variable	Different MB doses (175, 350, and 700 mg)	Different MB doses (175, 350, and 700 mg) and placebo	Different MB doses (175, 350, and 700 mg) and placebo	MB or Placebo consumption in a natural environment
Dependent variable	Sour, bitter, tart, and sweet taste perception ratings of food‐based solutions and individual food items	Ratings for sourness and bitterness taste perceptions, overall liking and intake of hypo‐palatable mixed vegetarian salad Ratings for sweetness taste perceptions and overall liking of SSBs	As mentioned in Phase 2	Primary outcomes Food preferences (Overall meal liking and preferences across time) Energy intake Dietary quality Other outcomes of interest Feasibility of the treatment protocol and study procedures Appetite Anthropometry/Body composition
Sample size	54	40	40	30
Proposed study period	1 July–30 September, 2024	1 November 2024–30 September 2025	1 December–30 June, 2025	1 May–30 December, 2025

*Note:* Sociodemographic characteristics (sex*, age, income, employment status, and education status), phenotypic taste perception, genotypic taste sensitivity, mouth pH, anthropometry, and body composition will be collected as covariates. In Phases 3 and 4, comorbidities (e.g., diabetes, hypertension) and medication use (self‐reported) will also be assessed. In Phase 4, physical activity will be measured as a covariate for secondary outcomes. *Sex is classified based on biological characteristics.

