### Sample Size

3.4

Table 1 summarizes the sample size for each phase and is determined based on previous effect estimates (Phase 1), the number of fixed‐effect factors to be considered in the regression model (Phases 2 and 3), and the recommended minimum sample size per treatment arm for feasibility studies (Phase 4, Table 2).

#### Phase 1

3.4.1

The sample size is calculated, considering an effect estimate (Cohen's d) of 0.78 from Wong and Kern (2011) on the sweetness taste perception obtained before and after taking MB using G*power software version 3.2, considering 80% power, α level of error of 0.05, and 20% dropout. Using paired sample *t*‐tests, 54 participants (18 in each group) will be recruited.

#### Phases 2 and 3

3.4.2

Determining sample size for mixed models (LMM/GLMM) is challenging, as statistical power depends on multiple factors, including the number of participants, repeated measures per subject, intra‐class correlation (ICC), outcome distribution, and the specified random‐effects structure (Kumle et al. 2021). Given uncertainties, particularly regarding predictors that will ultimately be retained as fixed effects in the final model, the sample size for this study is determined using an empirically informed approach. Consistent with Green (1991) guidelines for regression analyses, for behavioral research with expected large effect estimates, a minimum of 10 participants per predictor variable will be required for included to ensure model stability. In the planned mixed model, treatment (i.e., dose) will be specified as the primary fixed effect, time (pre‐post assessment) as the within‐subject factor, and participant as a random effect. Covariates such as age, sex, and phenylthiocarbamide (PTC) sensitivity will be considered for inclusion to control for potential confounding but will only be retained in the final model if they contribute meaningfully to model stability and fit. Based on an anticipated inclusion of four fixed factors in the final model, a minimum of 40 participants will be recruited for each study phase.

#### Phase 4

3.4.3

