2	To compare the effect of different doses of MB on sourness, and bitterness taste perceptions and overall liking of a hypo‐palatable mixed salad among healthy‐weight Australian adults	Different MB doses ○ Dose 1: ½ tablet (≈170 mg) ○ Dose 2: 1 tablet (≈350) ○ Dose 3: 2 tablets (≈700 mg) Placebo	Ratings for sourness and bitterness taste perception	gLMS (0–100)	As proposed in Phase 1 Additionally, as the sample size was determined using the empirical guideline of at least 10 subjects per predictor variable (Green 1991), and given the complexity in power estimation for mixed models, post hoc sensitivity power analysis will be conducted for planned comparisons. This will determine the minimum detectable effect size based on the achieved sample size and desired statistical power. Recent literature also recommends strengthening sample size justification for such approaches through sensitivity power analyses (Lakens 2022)
			Rating for overall liking	LAMS (0–100)	
			Intake	Served amount of salad minus left over	
	To compare the effect of different doses of MB on sweetness taste perceptions and overall liking of hyper‐palatable SSBs among healthy‐weight Australian adults	Different MB doses ○ Dose 1: ½ tablet (≈170 mg) ○ Dose 2: 1 tablet (≈350) ○ Dose 3: 2 tablets (≈700 mg) Placebo	Sweetness taste perception ratings	gLMS (0–100)	
			Ratings for overall Liking	LAMS (0–100)	
3	To compare the effect of different doses of MB on sourness and bitterness taste perceptions and overall liking of hypo‐palatable mixed salad among overweight or Obese Adults residing in Australia	Different MB doses ○ Dose 1: ½ tablet (≈170 mg) ○ Dose 2: 1 tablet (≈350) ○ Dose 3: 2 tablets (≈700 mg) Placebo	Ratings for sourness and bitterness taste perceptions	gLMS (0–100)	As proposed in Phase 2
			Ratings for overall liking	LAMS (0–100)	
	To compare the effect of different doses of MB on sweetness taste perceptions and overall liking of hyperpalatable SSBs among overweight/obese adults residing in Australia	Different MB doses ○ Dose 1: ½ tablet (≈170 mg) ○ Dose 2: 1 tablet (≈350) ○ Dose 3: 2 tablets (≈700 mg) Placebo	Ratings for sweetness taste perceptions	gLMS (0–100)	
			Ratings for overall Liking	LAMS (0–100)	

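### The 40 participants per phase in Phases 2 and 3 rest on four predictors that are not itemised and that count a four-level dose as one; the rule fits 40 only for a narrower model than the text describes

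*Protocol article*

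**What the plan says.** Section 3.4 opens by saying that Phases 2 and 3 are sized on the number of fixed-effect factors to be considered in the model. Section 3.4.2 sets the rule, citing a regression guideline: "a minimum of 10 participants per predictor variable will be required". It then describes the model:

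- Dose: "treatment (i.e., dose) will be specified as the primary fixed effect".
- Time (pre and post) is the within-subject factor, and participant is a random effect.
- Covariates: "Covariates such as age, sex, and phenylthiocarbamide (PTC) sensitivity will be considered for inclusion". They stay in the final model only if they help stability and fit.

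The conclusion, for each of the two phases, is: "Based on an anticipated inclusion of four fixed factors in the final model, a minimum of 40 participants will be recruited". The four factors are not listed.

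Table 1 gives the levels of the dose variable in both phases: "Different MB doses (175, 350, and 700 mg) and placebo". Section 3.7.3 allocates 10 participants to each of the four arms, and section 3.7.4 makes Phase 3 identical in design. Table 6 (section 3.8) carries the Phase 1 analysis over to Phases 2 and 3: dose as a fixed effect, time within subject, covariates chosen by model fit, main-effect tests, and Šidák-corrected pairwise comparisons between doses. It names no dose-by-time term. It repeats the sizing rule ("at least 10 subjects per predictor variable") and plans a post hoc sensitivity power analysis for the minimum detectable effect.

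**The concern.** The per-predictor rule is the only basis given for 40. No effect size, SD or power enters the calculation for these phases. The justification is therefore only as good as the count of four, and that count is doubtful in three ways. It is not itemised, in a paragraph that names five candidates. It treats a four-level dose, to be compared pairwise, as one predictor. And it has no room for a term that separates the effect of the tablet from the pre-tablet state.

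The last point matters most for the question asked. The pre-tablet rating is taken before anyone receives MB or placebo. A main effect of dose averages that untreated rating with the post-tablet one, and a main effect of time averages over all arms, placebo included. Neither isolates what a given dose did. A dose-by-time term does, and so does adjusting the post-tablet value for the pre-tablet value.

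These phases are meant to find an effective dose. If what 10 per arm can detect is not stated beforehand, a finding that no dose works cannot be told apart from a comparison that was too small.

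**Working it through.** **Inputs.** Rule of 10 per predictor, four anticipated factors, N = 40 and the named terms: section 3.4.2. Four dose levels: Table 1. Ten per arm: section 3.7.3. Pairwise Šidák comparisons and the 0.05 level: Table 6. Assumed here: 80% power (the article gives no value for these phases), all six pairs compared, and pre-post correlations of 0.5, 0.7 and 0.8 (the article gives none).

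**Step 1: the plan's own figure.** 4 × 10 = 40. It reproduces.

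**Step 2: counting variables.**
- Dose + time + two covariates = 4, so 40. The rule is met.
- Dose + time + all three named covariates = 5, so 50. At 40 this is 40/5 = 8 per predictor.

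**Step 3: counting coefficients.** Dose takes 4 − 1 = 3, time 1, dose-by-time 3 × 1 = 3, and each named covariate 1.

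| Model | Coefficients | N by the rule | Participants per coefficient at 40 |
|---|---|---|---|
| Dose + time | 3 + 1 = 4 | 40 | 10.0 |
| Dose + time + two covariates | 6 | 60 | 6.7 |
| Dose + time + three covariates | 7 | 70 | 5.7 |
| Dose + time + dose-by-time | 7 | 70 | 5.7 |
| The same + three covariates | 10 | 100 | 4.0 |
| Post value on treatment + pre value | 3 + 1 = 4 | 40 | 10.0 |

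The last row answers the dose question and meets the rule.

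**Step 4: what 10 per arm can detect, without baseline adjustment.** For two arms out of four with a pooled SD, df = 40 − 4 = 36, and the noncentrality is d × √(10/2) = 2.236 d. Solve for 80% power, two-sided.
- One uncorrected pair: α = 0.05, critical t = 2.028, required noncentrality 2.879, so d = 2.879/2.236 = 1.29 SD.
- Šidák over six pairs: α = 1 − 0.95^(1/6) = 0.00851, critical t = 2.784, required noncentrality 3.650, so d = 3.650/2.236 = 1.63 SD.

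**Step 5: with pre-tablet adjustment.** The residual SD shrinks by √(1 − r²), and one degree of freedom is spent (35 df). The unadjusted multipliers at 35 df are 1.289 and 1.635.

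| Assumed r | √(1 − r²) | One pair | Šidák, six pairs |
|---|---|---|---|
| 0.5 | 0.866 | 1.12 SD | 1.42 SD |
| 0.7 | 0.714 | 0.92 SD | 1.17 SD |
| 0.8 | 0.600 | 0.77 SD | 0.98 SD |

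The SD here is that of the post-tablet value within an arm.

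**The case against.** The strongest reply is that nothing has been miscalculated. The rule is worded per predictor variable and the forecast is in factors, so 4 × 10 = 40 is consistent. Age, sex and PTC sensitivity are candidates, and dose, time and two retained covariates make four. Even by coefficients, dose and time alone make exactly four. How the cited guideline treats multi-level factors cannot be checked from the article. The article also admits that mixed-model sizing is uncertain and plans a sensitivity power analysis.

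Much of this stands. A reader might infer that 40 breaks the article's own rule, or that the planned model has 7 to 10 predictors. The document supports neither. The range 7 to 10 requires counting coefficients instead of variables and adding a dose-by-time term that the article does not state. The figures 50, 60, 70 and 100 are therefore consequences of particular models, not requirements that the article sets itself.

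Three things are left. The section says that it sizes on factors to be considered, and the paragraph considers five. The two readings under which 40 fits are different models (main effects only, or dose counted once plus two unnamed covariates), and the reader is not told which is meant. And neither reading contains a term that isolates the effect of the tablet. The planned sensitivity analysis does not close the gap, because it is post hoc and based on the achieved sample; it cannot justify 40 in advance.

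It is also fair to object that 1.29 and 1.63 SD describe a comparison of post-tablet values alone, while the design has a pre-tablet value. Quoted by themselves they would overstate the problem, so they are given here with the adjusted range.

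**Conclusion.** The concern holds as a defect in the stated justification, not as an arithmetic error. The count of four is not itemised, sits beside five named factors, and treats a four-level dose as one predictor. By coefficients, 40 covers dose and time main effects and nothing more. With two or three covariates the same rule gives 60 or 70; with the unstated dose-by-time term it gives 70 to 100, or 5.7 down to 4.0 participants per coefficient at 40.

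In precision terms, 10 per arm detects about 1.29 SD (one pair) or 1.63 SD (Šidák, six pairs) without adjustment. With pre-tablet adjustment the ranges are 1.12 to 0.77 SD and 1.42 to 0.98 SD. These figures assume 80% power, a common SD, no dropout, all six pairs compared, and correlations of 0.5 to 0.8. Section 3.4.2 relies on large effects without giving a value. Section 3.4.3, in another context, classes large as 0.7 or more; an effect at the bottom of that class would fall short of 80% power in every case shown.

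**What to change.** In section 3.4.2 and the Phase 2 and 3 rows of Table 6:

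1. Keep 40 per phase, list the model terms, and say whether the rule counts variables or coefficients.
2. For the primary dose comparison, model the post-tablet value on treatment (3 coefficients) and the pre-tablet value of the same outcome (1). That is four coefficients, fits 40 under the rule, and targets the dose effect directly.
3. Label any model with further covariates (age, sex, PTC sensitivity) a sensitivity analysis, because it exceeds the rule.
4. State before the analysis what 10 per arm can detect with 80% power, with and without pre-tablet adjustment, over a stated range of correlations and for a stated number of Šidák-corrected pairs. Keep the post hoc sensitivity analysis as a supplement.

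The cost is a rewording of the two places and a change in the form of the primary model. No participants or measurements are added, since the pre-tablet values are already collected. The only downside is that the stated justification looks less favourable.

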### Participant Recruitment

3.5

Participants will be recruited using a convenience sampling technique. Recruitment will be advertised through Griffith University volunteer research broadcasts, social media platforms, and printed flyers displayed in various locations, including Griffith University premises (Gold Coast campus), medical centres, community centres, restaurants, places of worship, and leisure centres. Flyers will include the principal investigator's contact details (email) and a QR code for registration. In addition, recruitment strategies will include radio advertisements, direct in‐person/word‐of‐mouth approaches, and invitations to students enrolled in courses at Griffith University, Gold Coast campus. The recruitment plan is presented in Table S3.

### Data Collection Tools

3.6

Table 3 describes measurement tools for each key outcome variable and covariates in each project phase.

**TABLE 3 fsn371640-tbl-0003:** Measurement tools and their description for key variables in each phase of the project.

Phases	Variable to be measured		Tool	Description	References
Phase 1	Sour, bitter, tart and sweet taste perceptions of individual food‐based solutions and food items		Generalized Labeled Magnitude Scale (gLMS)	Ranges from 0 (barely detectable) to 100 (the strongest sensation of any kind). Participants will establish these boundaries (no sensation to strongest imaginable) before rating items	Green et al. (1996)
Phases 2 and 3	Overall liking of hypo‐palatable mixed vegetarian salad and hyper‐palatable SSB		Labeled Affective Magnitude Scale (LAMS)	Ranges from 0 (greatest imaginable dislike) to +100 (greatest imaginable like). Study participants will be asked, “How much do you like/dislike this food item? (please put a slash (/) mark somewhere on the line).”	Schutz and Cardello (2001)
	Sourness and bitterness taste perceptions of hypo‐palatable mixed vegetarian salad and sweetness taste perceptions of hyper‐palatable SSBs		Generalized Labeled Magnitude Scale (gLMS)	Ranges from 0 (barely detectable) to 100 (the strongest sensation of any kind). Before rating items, participants will establish these boundaries (no sensation to the strongest imaginable)	Green et al. (1996)
	Intake of the hypo‐palatable mixed vegetarian salad		The difference between the amount served and the amount left over	At both the pre‐test and post‐test sessions, participants will be provided with a fixed portion of mixed salad weighing 117 g, which corresponded approximately to half a serve of vegetables and half a serve of fruit according to the Australian Dietary Guidelines. Participants will be instructed to consume as much of the provided salad as they desired. Each portion will be weighed prior to serving, and any leftovers will be weighed immediately after consumption. Actual intake will be calculated as the difference between the amount served and the amount remaining	National Health and Medical Research Council (2013)
Phase 4	Change in the food preferences in a natural environment (i.e., at home)		Food‐liking questionnaire (FLQ)	FLQ is validated for the Australian population and contains 73 food items. It measured liking using a nine‐point hedonic scale, in which ‘like extremely’ was coded as ‘9’ and ‘dislike extremely’ was coded as ‘1’. If participants have never eaten a particular food or never experienced one of the listed items, they will be instructed to rate the item as “neither like nor dislike”. At baseline, sixth‐ and 12th‐week participants will score their liking of all listed food items in the FLQ. In the FLQ foods, items are grouped into 10 main categories based on the Australian Guide to Healthy Eating: grains, vegetables, fruits, dairy, animal‐based protein, plant‐based protein, fat and oil, sweet food, salty food, and alcohol. The mean in food‐liking scores for each food category will be generated (Wanich et al. 2020). Finally, the change in mean liking score for each food group, and the total change in food liking score, will be analyzed across measurement sessions	Wanich et al. (2018)
	Change in the overall liking of the specific or mixed food as a meal (breakfast, lunch, dinner, snack) in a natural environment (i.e., at home)		Any perceived change will be recorded using a yes/no response, and its magnitude will be quantified using Labeled Affective Magnitude Scale (LAMS)	Participants will record whether there is a perceived change in overall liking of meals due to the tables (yes/no). Then using LAMS, in which 0 represents the greatest imaginable dislike, and + 100 represents the greatest imaginable like, they will rate their liking of that specific meal. The scale will include options to select the meal type (breakfast, lunch, dinner, snack), a space to note down the major meal constituents, a space to attach photos of the meal (photo of a meal before and after eating, and the date and the time the meal was consumed)	Schutz and Cardello (2001)
	Perceived change in appetite		Perceived change in appetite (yes, no), and the direction of change (increase appetite or decreased appetite)	Along with the change in overall liking of meals, participants will note the effect of the tablet on their appetite (whether it helps them eat less, causes no change, or makes them eat more)	
	Change in energy intake		A 3‐day food record method	Dietary intake will be collected at baseline, sixth, and 12th weeks. Then, the quantity and type of food items consumed will be changed to calorie intake and macronutrient intake (carbohydrates, proteins, total fat, saturated fat) using the AUSNUT 2011–2013 food composition database (Grech et al. 2017)	Bailey (2021)
			24‐h dietary recall method	At each visit, the 3‐day food record and the Australian Recommended Food Score (ARFS) will be supplemented with the 24‐h dietary recall (24 h) method to comprehensively assess dietary intake. The 24HR will be conducted through structured interviews to collect detailed information on all foods and beverages consumed in the preceding 24 h. Portion sizes will be estimated using food models, household measures, or standardized references, and nutrient intake will be analyzed using the AUSNUT 2011–2013 food composition database. Dietary quality indices will be determined by categorizing consumed foods into predefined food groups. To account for variability in dietary intake, two non‐consecutive 24HRs, one on a weekday and one on a weekend day, will be collected at baseline, week 6, and week 12	Castell et al. (2015)
	Change in dietary quality		Australian Recommended Food Score (ARFS) questionnaire	The ARFS is derived from the Australian Eating Survey food frequency questionnaire but focuses on the 70 questions related to nutrient‐dense core foods as classified by the Australian Dietary Guidelines. The ARFS includes eight sub‐scales: vegetables (*n* = 21), fruit (*n* = 12), meat (*n* = 7), non‐meat/flesh protein foods (*n* = 6), breads and cereals (*n* = 13), dairy foods (*n* = 11), water (*n* = 1), and spreads and sauces (*n* = 2). The total ARFS score ranges from 0 to 73, calculated by summing the points for each food item from different food groups. Changes in the total ARFS score or changes in the scores of the eight food groups will be compared between the MB and placebo groups	Collins et al. (2014, 2015)
	Physical activity as a covariate		International Physical Activity Questionnaire (IPAQ)	Physical activity will be measured using the short form of the International Physical Activity Questionnaire (IPAQ). The short, self‐administered format is designed to assess physical activity during the previous 7 days across four domains: vigorous activity, moderate activity, walking, and sitting time. It consists of seven questions and will provide estimates of the frequency (days per week) and duration (minutes per day) of activities	Craig et al. (2003)
All phases	Anthropometry	Height	Portable stadiometer (Model No. Seca 213)	The stadiometer will be mounted upright on a labeled, hard surface. Participants will take off their shoes and socks and stand straight, with their heads aligned in the Frankfort plane and their heels, buttocks, upper back, and occiput touching the stadiometer	Kobel et al. (2022); WHO (1995)
		Waist circumference	Non‐stretchable measuring tape (seca‐201 Tape)	Measured at the midpoint between the iliac crest and lower costal border, just above the level of the umbilicus. The subject stands with arms folded across the chest and is measured at the end of normal expiration. Tapes will be regularly inspected to ensure it is not bent or damaged.	Mason and Katzmarzyk (2009)
	Body composition (Body weight, BMI, Fat mass, fat‐free mass, body fat percentage, body water)		Bioelectrical impedance analysis (BIA) (Model No. BC‐541)	BIA measures body composition by sending a small electric current (50 kHz) through the body and measuring the tissue resistance encountered (Marra et al. 2019). The assumption is that the current travels more easily through lean tissue containing more water than fat tissue. It is valid in estimating body fat percentage (R^2^ = 0.92 compared to DXA) (von Hurst et al. 2016). In this study, we will use BIA Model No. BC‐541, the person will stand barefoot on the device's footplates and grasp the handles. Before attending the lab, participants will be instructed to refrain from consuming alcohol and avoid vigorous physical exercise (24 h) and not eat or drink anything 1 h before the test. Within the lab, participants will be asked to remove all metal objects and jewelry, and they will be asked if they have any electrical devices, like a pacemaker. For measuring weight, participants will be instructed to wear light clothing and remove footwear	Kyle et al. (2004)
	Phenotypic taste sensitivity		PTC paper strips	Measured by placing PTC strips on the tongue. Individuals who report the PTC strip as bitter will be categorized as tasters, and those who do not taste bitterness will be categorized as non‐tasters (Veluswami et al. 2015)	Veluswami et al. (2015)
	Genotypic taste sensitivity		*TAS2R38* gene from saliva	Saliva samples will be collected using OG‐500 Oragene•Dx kits (2 mL). Participants will rinse their mouths with water before sampling (Garbieri et al. 2017). TAS2R38 gene will be measured via PCR after DNA extraction. Common haplotypes such as PAV (Proline‐Alanine‐Valine), AVI (Alanine‐Valine‐Isoleucine), and PAV/AVI will be identified (Negri et al. 2015)	Robino et al. (2022)
	pH of the mouth		pH paper strip	Participants will spit their saliva into a disposable cup provided and be guided to place the pH paper strip in the saliva. Then, the researcher will determine the pH based on the color change of the pH paper	Aoyama et al. (2017)
	Sociodemographic variables		Sociodemographic questionnaire	Age, sex, income, educational status, and occupational status will be collected using a sociodemographic questionnaire based on the Australian Bureau of Statistics. The questionnaire will incorporate associated comorbidities and the type of current medication intake	ABS (https://www.abs.gov.au/)

